### Ranking Selection Component

The ranking/selection component of the design compares the response rates between the treatment groups, and selects the treatment regimen with the best response rate, irrespective of how large or small the advantage over the others may be. The sample size in such a selection design is selected to assure that if one of the treatments has an underlying response rate which is clearly superior to that of the other treatments; it will be selected with high probability. FONT II includes a sample size of 42 (up to 53 patients may be enrolled in the galactose arm to ensure a subgroup of 42 with a P_alb _> 0.5) patients in each of the 3 treatment groups for a total sample size of 126. This will insure that the treatment with the best response rate will be correctly selected with a probability of 85% if one of the treatments has a response rate ≥40% and all the remaining treatments have response rates no higher than 25%.

### Subgroup Analysis

It is anticipated that approximately 80% of the enrolled patients will have P_alb _> 0.5. This value represents the lower limit for increased levels of the permeability factor, which is the putative target of galactose treatment. Therefore, a secondary analysis will be performed in which the response rate of the Galactose arm will be computed separately for the subgroup with P_alb _> 0.5. The ranking-selection comparison of all three groups will also be repeated in patients with P_alb _> 0.5.

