Published reports indicate that serum samples of nearly 50% of patients with primary steroid resistant FSGS have the capacity to increase the permeability of glomeruli to albumin, (P_alb_) during *in vitro *incubation and testing [23]. Standard conditions for these studies include incubation of glomeruli from normal rats with medium containing 2% vol/vol patient serum. A value of to ≥ 0.5 is defined as a positive test [24]. Addition of 10^-12 ^M galactose to the incubation medium containing patient serum completely prevents the increase in permeability. Removal of galactose by extensive dialysis of the medium restores P_alb _activity. Intravenous administration of galactose or chronic ingestion of galactose prior to obtaining serum markedly decreases P_alb _activity. Dialysis of sera obtained after galactose administration does not restore activity, suggesting that galactose enhances removal of a circulating permeability factor [25]. Savin and colleagues have postulated that increased hepatic clearance by galactose-binding proteins (galectins) may be responsible for removal of the permeability factor. There are case reports describing individual patients with FSGS who were given oral galactose for over 6 months and who demonstrated reduction in P_alb_, lowering of proteinuria, and stabilization of kidney function [26]. These findings raise the possibility that extended administration of galactose to lower P_alb _in patients with resistant FSGS may reduce proteinuria and delay progressive decline in kidney function [27].

The FONT trial (DK70341) is a combined Phase I/II project with an overall objective to identify promising new antifibrotic agents for further testing and distinguishing them from agents which are likely to be ineffective. A staged approach to drug evaluation is incorporated into the Phase II trial design to avoid large expenditures on unworthy and untested therapeutic agents for this serious disease.

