### Study Population

Inclusion and exclusion criteria for enrollment are defined in Table 1. The eligibility criterion for steroid resistance or intolerance is defined in recognition of a reluctance of nephrologists to routinely administer a prescribed course of corticosteroids to all patients because of the potential for serious adverse events. FSGS can occur as a consequence of genetic mutations in structural proteins in the podocyte [33-36]. Thus, confirmation of a disease-causing mutation in a podocyte protein is an eligibility criterion for the FONT II trial in patients who lack biopsy-confirmation of the diagnosis of FSGS. Although there is a lack of data on expected response rates to antifibrotic therapy in the presence or absence of podocyte mutations, progressive renal fibrosis is an intrinsic feature of primary FSGS, regardless of whether or not there is a defined genetic mutation. In any event, DNA specimens for storage in the NIDDK Biorepository will be obtained from all patients who enroll in the trial and consent to the procedure. There is no exclusion criterion based on obesity because antifibrotic agents should also be beneficial in patients with obesity-related FSGS.

**Table 1 T1:** FONT II Study Eligibility Criteria

Inclusion Criteria
1. Primary FSGS confirmed by renal biopsy

2. Failure to respond to prior therapy with at least one of the following immunosuppressive medications -- cyclosporine, tacrolimus, mycophenolate mofetil, sirolimus - or other agents prescribed to lower proteinuria

3. Age 1-50 years at onset of proteinuria

4. Age 1-51 years at time of randomization

5. Estimated GFR ≥40 mL/min/1.73 m^2 ^using Schwartz (age <18 yr) or Cockcroft-Gault (age ≥ 18 yr) formula at screening and ≥30 mL/min/1.73 m^2 ^at the end of the Run-In Period and prior to randomization

6. Up/c > 1.0 g protein/g creatinine on first morning void

7. Steroid resistance defined as failure to achieve sustained Up/c < 1.0 following a standard course of prednisone/prednisolone/methylprednisolone prescribed for FSGS therapy, OR contraindication/anticipated intolerance to steroid therapy defined as severe obesity, documented decreased bone density, family history of diabetes, or a psychiatric disorder.

8. Willingness to follow the protocol, including medications, baseline and follow-up visits, and procedures.

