### Statistical Considerations, Efficacy and Power

A hybrid Phase II design as described by Liu et al [37] will be used which incorporates a ranking/selection comparison [38,39] between the treatment groups as well as a minimum activity requirement within each treatment group. FONT II will include a sample size of 42 patients in each of the three treatment arms, with a total sample size of 126 patients. Up to 53 patients may be enrolled in the galactose arm (137 total subjects) to ensure a subgroup of 42 with a P_alb _> 0.5. Although the galactose arm was added after initiation of the study, patient enrollment was very low prior to this change. Therefore, introduction of galactose and removal of rosiglitazone are not anticipated to influence the study population. We next describe the assessment of the minimum activity requirement and the ranking/selection components of the study.

Minimum efficacy component: A two-stage procedure will be conducted to determine if the individual novel experimental treatments achieve a minimal level of efficacy that would signify that the therapies are sufficiently promising to warrant further investigation. In the first stage, patients will be enrolled until each of the 3 treatment groups has accumulated 17 randomized subjects. At this point, randomization will be temporarily halted, and there will be a 6 month pause during which the first set of patients assigned to each of the 3 arms will be allowed to complete the treatment period and have their response to the therapy evaluated. If in either of the experimental groups - adalimumab or galactose groups-- there are one or fewer responders among the first 17 randomized patients, that group will be dropped from further consideration. After the 6-month pause, the study will resume randomization until 42 patients (up to 53 patients may be enrolled in the galactose arm to ensure a subgroup of 42 with a P_alb _> 0.5) are accrued for each agent that passed the initial efficacy threshold.

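### A cap of 53 galactose patients does not ensure 42 with P_alb > 0.5, and the 80% prevalence behind it is not reconciled with the nearly 50% in the Background

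*Protocol article*

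**What the plan says.** The base design in Statistical Considerations, Efficacy and Power reads: "FONT II will include a sample size of 42 patients in each of the three treatment arms, with a total sample size of 126 patients". The same section then enlarges one arm: "Up to 53 patients may be enrolled in the galactose arm (137 total subjects) to ensure a subgroup of 42 with a" P_alb > 0.5. The Ranking Selection Component section repeats the allowance and the claim.

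The Subgroup Analysis section supplies the prevalence: "It is anticipated that approximately 80% of the enrolled patients will have" P_alb > 0.5. It plans two secondary analyses: the galactose response rate within that subgroup, and a repeat of the three-arm ranking restricted to it. It gives no source for the 80%.

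The Background cites published reports that "serum samples of nearly 50% of patients with primary steroid resistant FSGS have the capacity to increase the permeability of glomeruli to albumin". Shortly afterwards it says that a value at or above "0.5 is defined as a positive test".

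Table 1 (Study Population) admits patients on steroid resistance, "Steroid resistance defined as failure to achieve sustained Up/c < 1.0 following a standard course of prednisone/prednisolone/methylprednisolone prescribed for FSGS therapy", or on a contraindication to or anticipated intolerance of steroids. It also requires failure of other therapy and Up/c above 1.0. It contains no P_alb criterion.

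**The concern.** There are two separate difficulties.

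First, a cap set by dividing the target by the anticipated proportion delivers the target on average. It does not ensure it. Because 53 is a maximum, the text offers no way to continue until 42 P_alb-positive patients have accrued.

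Second, the 80% stands beside a much lower figure in the same article, for a closely similar population and apparently the same test. If the lower figure applied to the trial, the target subgroup could not be reached.

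This matters because the subgroup is the only stated reason for the 11 extra galactose patients, and because the permeability factor is described as the putative target of galactose. The ranking is also to be repeated in the subgroup, yet the other two arms stay at 42 in total. Their P_alb-positive subgroups will therefore be smaller than 42 at either prevalence, and the article does not say how small.

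**Working it through.** **Inputs.** Target subgroup 42, cap 53, base 42 per arm, totals 126 and 137 (Statistical Considerations, Efficacy and Power). Prevalence 80% (Subgroup Analysis). Nearly 50% (Background), taken as 50%. Selection scenario of 40% against 25% and 25%, with a stated selection probability of 85% (Ranking Selection Component).

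**Step 1: reproduce the cap.** 42 / 0.80 = 52.5, rounded up to 53. The extra patients number 53 − 42 = 11, and 126 + 11 = 137. Both of the article's figures are reproduced, so the 53 is an expectation calculation at 80%: 53 × 0.80 = 42.4.

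**Step 2: the chance of reaching 42.** Let X be the number with P_alb > 0.5 among 53 galactose patients, X ~ Binomial(53, p). P(X ≥ 42) is also the chance of reaching 42 if enrolment stops early once 42 are found.

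| Prevalence p | Expected 53p | P(X ≥ 42) |
|---|---|---|
| 80% | 42.4 | 63.3% |
| 75% | 39.75 | 29.6% |
| 70% | 37.1 | 9.1% |
| 60% | 31.8 | 0.24% |
| 50% | 26.5 | 0.001% (1.1 × 10⁻⁵) |

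At the article's own 80% there is a 36.7% chance of falling short. For 53 patients to give an 80%, 90% or 95% chance of 42, the prevalence would have to be about 83%, 85% or 86%.

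**Step 3: comparator arms in the repeated ranking.** Each stays at 42 patients. The expected number with P_alb > 0.5 is 42 × 0.80 = 33.6 (about 34) at 80%, and 42 × 0.50 = 21 at 50%.

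**Step 4: selection probability.** For the full design with 42 per arm and 40% against 25%/25%, exact enumeration gives 85.6% if the best arm must win outright (88.0% if ties are split at random). The first figure agrees with the article's 85%.

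For the subgroup, the ranking was simulated with subgroup sizes drawn at random: galactose stopped at 42 positive or 53 in total, and the other arms had 42 patients each. The results, whether the best arm is galactose or a comparator, are:

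- 80% prevalence: about 85–86%
- 50% prevalence: about 77–78%

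Exact values with sizes fixed near their expectations and ties split are close: 86.1% for 42/34/34 and 78.6% for 26/21/21, with galactose best.

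**The case against.** **The arithmetic is right.** The 53 follows correctly from 80%, the text says *up to* and *approximately*, and sizing on an expectation is ordinary practice. This stands: there is no calculation error. At 80% a shortfall would also usually be small, because the 5th percentile of Binomial(53, 0.8) is 37 and the 25th is 40. But the article claims assurance, twice, and a 63% chance is not assurance.

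**The two prevalences may describe different things.** The Background does not expressly say that nearly 50% exceed 0.5; the figure and the cut-off come in separate sentences with separate citations. The trial also requires failure of other therapy and admits steroid-intolerant patients. A condensed article may leave the source of the 80% to the full protocol. All this is fair, and it means that 50% cannot be taken as the trial's true prevalence. It does not remove the need to reconcile two figures printed in the same article, when no eligibility criterion selects on P_alb.

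**Stronger readings that the article does not support.** A reader might infer that the stated 85% selection probability fails in the subgroup. At 80% prevalence it does not: it is still about 85–86%, even with about 34 patients per comparator arm. A reader might also infer that the rule of at least 9 responders in 42 would be applied to a smaller subgroup, with a loss of power. The article states that rule for the full treatment groups; for the subgroup it promises only a response rate and a repeated ranking. Neither inference forms part of this point, and no table of subgroup thresholds is needed.

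**Conclusion.** The claim that 53 galactose patients ensure 42 with P_alb > 0.5 is wrong as written. Under the article's own 80% the chance is about 63%, and it falls quickly below that prevalence. The 80% is unsupported in the text and unreconciled with the nearly 50% in the Background. If the trial's prevalence were about 50%, the subgroup would number 26 to 27, 42 would be practically unreachable, and the selection probability in the repeated ranking would fall to about 77–78%.

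The binomial results assume that patients' P_alb status is independent with a common prevalence. The 50% results further assume that the Background figure applies to enrolled patients at the 0.5 cut-off, which the article does not establish.

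The scope is limited to a secondary subgroup analysis and 11 optional galactose patients. The primary endpoint, the two-stage error rates and the main ranking do not depend on it. The point should still be corrected, because a stated sample size is not delivered by the design and the correction is easy.

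**What to change.** 1. In Subgroup Analysis, give the basis for the 80% and explain how it relates to the nearly 50% in the Background (for example, a different population or a different definition of a positive test), or revise it.
2. In Statistical Considerations, Efficacy and Power and in Ranking Selection Component, replace *ensure* with the expected subgroup size and its probability: about 42, with a 63% chance of reaching 42, at 80% prevalence; about 26 to 27 at 50%.
3. For the repeated ranking, state that each comparator arm would have about 34 patients with P_alb > 0.5 at 80% prevalence or 21 at 50%, with a selection probability (40% against 25%/25%) of about 85–86% or 77–78%.

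The cost is a few sentences. No extra enrolment is needed, and the only loss is a less favourable stated subgroup size.

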### Ethics of Human Subject Research

The use of the full array of experimental therapies in the FONT Phase II Trial has been authorized by the FDA (IND # 100,037). The study protocol, design and consent forms have been approved by Institutional Review Board (IRB) at the two clinical coordinating centers - Cohen Children's Medical Center of New York and University of Michigan-CS Mott Children's Hospital - and 13 other participating sites (Nationwide Children's Hospital, Boston Children's Hospital, Oregon Health Sciences Center, Miami Children's Hospital, Carolinas Medical Center, Stollery Children's Hospital, Medical University of South Carolina, Emory University, Texas Tech University Health Sciences Center, Children's Mercy Hospital, University of Kansas, Mayo Clinic, and Cincinnati Children's Medical Center). Specific study elated information will be made available to the Food and Drug Administration (FDA) and the National Institutes of Health (NIH). All procedures will be in compliance with Health Information Portability and Accountability Act (HIPAA) regulations. The trial is funded primarily by the National Institutes of Health-NIDDK (DK70341) with a small supplemental grant from the NephCure Foundation. The project is listed at ClinicalTrials.gov with the identifier NCT00814255.

## Discussion

FSGS is a clinical entity with a distinctive histopathological appearance, which is either primary or secondary to other etiologies. This lesion accounts for 10-20% of cases of primary nephrotic syndrome in children and up to 35% of cases in adults. In the majority of patients, the primary lesion is refractory to therapeutic interventions with immunosuppressive agents. The final common pathway for advancing disease in primary FSGS is progressive fibrosis leading to ESKD, which occurs in 50 to 75% of patients over a 10-year period [1,2,40-42]. The morbidity and mortality of patients with FSGS is compounded by that of superimposed ESRD. The life expectancy for a 10-year old child who is dialysis-dependent is reduced by approximately 30 to 50 years from the current 84 years in the general US population. Following renal transplantation for FSGS, a high recurrence rate results in a 20-25% allograft loss and further diminishes the likelihood of long-term graft and patient survival. Thus, the longevity of patient survival is directly linked to success in treating FSGS and prolonging native kidney survival [43-45].

The lack of adequate RCTs has hindered clinical research in the treatment of FSGS. The majority of studies that have evaluated potential therapies for FSGS have either been uncontrolled, had poorly defined end-points, or had treatment periods of insufficient length [1,46]. This has engendered a great deal of controversy about the optimal treatment of FSGS and variability in practice from the onset of disease and throughout its course. Cyclosporine is the only drug that has been evaluated and demonstrated by RCT to be useful in pediatric and adult patients [1,2]. The lack of effective agents if cyclosporine fails is underscored by the observation that only 1 out of 14 invited articles dealing with FSGS described alternative treatments, most of which had only been studied in small uncontrolled patient cohorts [47].

This report describes an RCT whose objective is to evaluate potential efficacy of novel therapies that target reduction in renal fibrosis as their main mechanism of action. While this may be an off-target mechanism relative to the approved indication for the test agents, reduction in fibrosis is primary effect in the context of FSGS. However, a major challenge for this type of trial is the development of a dynamic study design aimed at efficiently identifying novel therapeutic approaches and on avoiding large expenditures on unworthy and untested therapeutic agents for serious diseases. The novelty of this project centers on the application of a distinct two step analysis of outcomes to expedite the identification of agents suitable for Phase III testing in patients with a rare glomerular disease, namely treatment-resistant FSGS.

Rosiglitazone was evaluated in the FONT I project [29] and was originally included as a treatment arm in the FONT II trial based on ample preclinical evidence that this drug has antifibrotic properties. However, recent meta-analyses of clinical trials in adults with type 2 diabetes suggest that treatment with thiazolidinediones is associated with an increased risk of myocardial infarction and possibly with overall cardiovascular morbidity and mortality [48,49]. It is unclear if this adverse effect is unique to rosiglitazone or is a class effect that also impacts on the use of the related agent pioglitazone. Although patients with primary FSGS differ from those with type 2 diabetes making it difficult to generalize the risk of serious adverse events from the latter to the former group, concerns about the feasibility of timely recruitment into the FONT Phase II trial forced abandonment of the rosiglitazone arm, leaving a 3-arm study that compares conservative medical therapy, adalimumab, and galactose. The study incorporates comprehensive surveillance for cancer detection because of the increase risk of malignancy in patients treated with TNF-α antagonists [50].

Because of the low incidence and prevalence of patients with FSGS, an efficient and productive study design that fosters collaboration is essential to implement cost-effective trials and to identify and recruit clinical subjects in a timely manner. While conducting Phase I studies, the FONT consortium developed a functional infrastructure that will sustain collaboration. This should hasten the successful performance of studies seeking to develop new therapeutic interventions that will improve the care and outcome of patients with FSGS. The support of the NephCure Foundation, which is dedicated to advancing research into the pathogenesis and treatment of FSGS, has facilitated the creation of the cooperative network and fostered awareness and enthusiasm for the study among patients and their families.

It is anticipated that the proposed clinical trial methodology will overcome existing difficulties involved in the study of rare kidney diseases by implementing cost-effective approaches aimed at identifying novel therapeutic approaches and by avoiding large expenditures in the evaluation of unworthy and/or unsafe therapeutic agents for serious glomerular disorders like FSGS.
